### Discontinuation of the Clinical Trial

The principal investigator and subinvestigators will take measures described below during the trial. If the trial itself is to be discontinued, the principal investigator and subinvestigators should maintain the safety of the subjects and take other appropriate measures. Reasons for discontinuation and any adverse events should be identified and recorded in the original documents and on the electronic case report forms. Tests and analyses that are scheduled at discontinuation will be performed as far as practical.

1) The Independent Data Monitoring Committee will be convened to review appropriateness of continuance of the trial, if adverse events of the following types occur: one or more serious adverse events regardless of causality; or two or more severe adverse events for which a causal relationship with the investigational products cannot be ruled out.

2) The clinical trial will be discontinued if serious adverse events for which a causal relationship with the investigational products cannot be ruled out occur during the trial and fall under either of the following conditions: two or more subjects aged below 18 experience severe adverse event(s); or a subject aged below 18 experiences three or more adverse events. The trial can be continued, however, if the Independent Data Monitoring Committee concludes that there is clear justification and means to maintain safety of remaining subjects.

# Independent Data Monitoring Committee

## Establishment of the Independent Data Monitoring Committee

In this clinical trial, an Independent Data Monitoring Committee shall be established for assessment of safety. The composition of committee members, matters to be assessed, and assessment criteria are to be arranged in accordance with procedures for the Independent Data Monitoring Committee separately prescribed.

## Purpose of the Independent Data Monitoring Committee

The Independent Data Monitoring Committee will be organized by the principal investigator to review appropriateness of continuance of the clinical trial to ensure reasonable safety of subjects.

## Assembly of the Independent Data Monitoring Committee

[Calling committee meetings]

If any of the significant matters listed below occurs, the principal investigator will promptly request the chair of the Independent Data Monitoring Committee to call a committee meeting to review appropriateness of continuance of the trial and other related matters.

1) Discovery of new significant information on safety concerning the investigational products of the trial

2) Serious adverse events in the trial, regardless of causality

3) Recognition of new, significant information on safety derived from similar products, research reports, or other sources

4) Other matters that the principal investigator deems essential

## Meeting Format and Discussion Materials for the Independent Data Monitoring Committee

The meetings of the Independent Data Monitoring Committee will be convened with the participation of all committee members, including participation via the Web.

The sponsor investigator will submit the materials below to the Independent Data Monitoring Committee for discussion.

[Materials for a primary discussion]

Any of the following materials as appropriate:

1) Reports concerning serious adverse events (Form 12)

2) Reports concerning discontinuation of production, recall, or disposal of the investigational products abroad

3) Summary of the latest report on the safety of the investigational products

4) Investigational products, side effects, and case reports in Japan

5) Individual Report Common Line Listing; and a list of unexpected and serious adverse drug reactions

6) Significant updates on safety information of similar products from research publications or other materials

7) Other information of which the sponsor investigator requested assessment

8) Reports on severe adverse events. This may be replaced by copies of the electronic case report forms.

[Materials for a secondary discussion]

Any of the following materials as appropriate, in addition to the materials for the primary discussion:

1) Copies of electronic case report form pages containing adverse events, vital signs, and clinical test results after the completion of SDV of cases registered

2) Data on blood concentrations of sirolimus

3) A duplicate copy of a report for partial unblinding of the emergency key codes

4) Other information as committee members deem required

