With regard to the blood concentration of sirolimus, any person involved in the trial, with the exception of the unblinded doctor and unblinded clinical research coordinators (CRCs), will follow the procedures for prescription of investigational products to ensure blindness to the test results is maintained. The test results will be reported to the Independent Data Monitoring Committee and the principal investigator, however, after the blind is broken or if the principal investigator so directs in case of emergency. The unblinded CRCs will assist in the work of the unblinded doctor and make sure that the dosage change based on trough concentration measurements is appropriately instructed.

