# Administration of Investigational Products

Figure 1 Dosing Protocol

Phase I (single-blind): NPC-12T placebo tablets for 3 months (12 weeks)

Phase II (double-blind): NPC-12T active substance tablets or NPC-12T placebo tablets for 6 months (24 weeks)

[Dosage at the outset of the trial]

Subjects weighing less than 40 kg will take one 1-mg tablet orally once every other day.

Subjects weighing 40 kg or more will take one 1-mg tablet orally once per day.

The investigational products are to be taken before sleep.

The bodyweight measured at V1 will be referred to in determining dosage throughout the trial.

<Rationale for the dosing time>

The package insert of Rapamune 1 mg tablets was referred to when setting the dosing time. The insert cites reports that state administration of the tablet after a high-fat meal increased the blood concentration of sirolimus. To reduce effects of high-fat meals, the dosing time of the investigational products is set to be before sleep.

[Prescription of the investigational products]

In Phase I (V1, V2, V3, and V4) and Phase II (V5 and V6), the principal investigator or subinvestigator will prescribe investigational products in accordance with the dosage at the start of the trial described above.

In Phase II (V7, V8, V9, V10, and V11), the unblinded doctor will instruct the principal investigator and subinvestigators on the prescription of the investigational product based on the criteria for dosage change. The principal investigator or subinvestigator will make a judgment on whether dosage reduction is required or dosage increase is permissible, taking account of subjects’ safety, including risks of adverse events. If the conditions are deemed appropriate, the principal investigator or subinvestigator will prescribe the investigational products as instructed by the unblinded doctor. The unblinded doctor will provide instructions to the principal investigator or subinvestigator in accordance with the trough concentration measurements and the prescription schedule generated by the randomization manager. The trough concentration measurements and the prescription schedule are not to be disclosed to any person except the unblinded CRCs until the end of the trial, and will be kept securely locked in a cabinet accessible only to the unblinded doctor.

[Criteria for dosage change]

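### The protocol gives three conflicting rules on who may receive sirolimus concentrations during the trial, and the route to the IDMC could unblind the investigator

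*Protocol*

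**What the plan says.** Three places in the Protocol govern who may see sirolimus concentrations.

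- **Administration of Investigational Products**, repeated in the Protocol Summary: the trough measurements and the prescription schedule "are not to be disclosed to any person except the unblinded CRCs until the end of the trial". They stay locked away under the unblinded doctor's control. No exception is given for the IDMC or for an emergency.
- **Randomization and Blinding**, item 3: "any person involved in the trial, with the exception of the unblinded doctor and unblinded clinical research coordinators (CRCs), will follow the procedures" that keep the results blinded. An exception follows: "The test results will be reported to the Independent Data Monitoring Committee and the principal investigator, however, after the blind is broken". The same sentence adds a second ground, an emergency release at the principal investigator's direction.
- **Section 15.4**: "The sponsor investigator will submit the materials below to the Independent Data Monitoring Committee for discussion". The list for a secondary discussion is introduced as "Any of the following materials as appropriate, in addition to the materials for the primary discussion", and its second item is "Data on blood concentrations of sirolimus".

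A fourth place is relevant. The section Procedure for Concealing and Unblinding Randomized Code already provides emergency unblinding of the subject in question, with the emergency contact center informing the principal investigator.

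**The concern.** In a placebo-controlled trial of sirolimus, a sirolimus concentration is close to a treatment code. The protocol goes to some length to protect it: an unblinded doctor, unblinded CRCs, and dose changes scheduled in advance for placebo subjects so that titration does not reveal the arm. Section 15.4 then makes the sponsor investigator the sender of a package that may contain these concentrations, and names no closed route and no part for the unblinded doctor.

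At stake is the blind of the person who, by context, decides whether an adverse event is related to the product. A related event is a side effect (14.10.4), and side effects are the second primary endpoint. Causality also enters the criteria for discontinuing the trial (14.11.2 and 15.5). The investigators also judge whether a dose increase is permissible or a reduction is required.

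**Working it through.** No stated figure bears on this point, so the check sets the passages side by side.

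**1. The rules compared**

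| Place | Who may receive | Condition | Limited to one subject? |
| --- | --- | --- | --- |
| Administration of Investigational Products; Protocol Summary | Unblinded CRCs (the unblinded doctor holds the data) | Until the end of the trial, no exception | Not applicable |
| Randomization and Blinding | IDMC and principal investigator | Blind broken, or emergency at the principal investigator's direction | Not stated |
| 15.4 | IDMC, with the sponsor investigator as sender | Secondary discussion, as appropriate | Not stated |
| Procedure for Concealing and Unblinding Randomized Code | Principal investigator (assignment, not concentration) | Urgent need to know the treatment, or pregnancy | Yes |

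**2. Where they conflict**

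- First against second row: the emergency release is allowed in one and barred in the other. The broken-blind release conflicts only if it covers a code broken for a subject during the trial. If it means the general unblinding after database lock, it does not.
- First against third row: supplying concentrations to the IDMC mid-trial is barred in one and foreseen in the other.
- Second against third row: 15.4 does not repeat the condition in the blinding section. A reader of 15.4 alone would not know that one exists.
- Second against fourth row: emergency unblinding by key code covers one subject. The emergency release of concentrations has no such limit.

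**3. What a listing would show**

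Earlier use of mTOR inhibitors is excluded and concomitant use is prohibited, so placebo subjects should have no measurable sirolimus. Section 14.8 schedules samples at V5 to V12, which is 8 visits. Phase II product is first prescribed at V5 and is taken before sleep, so the V5 sample should precede any active dose. That leaves 8 − 1 = 7 scheduled visits (V6 to V12) at which a result would point to the arm, and one such result per subject would normally be enough. A mid-trial listing would therefore inform on subjects already sampled on Phase II dosing, and on no others.

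**4. Who would be exposed**

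- The trial is investigator-initiated. The principal investigator organizes the IDMC (15.2) and requests its meetings (15.3). The sponsor investigator of 15.4 is reasonably that person.
- Section 14.10.4 names no causality assessor. But the electronic case report form is itself the source for causality (18.5), CRCs may enter only transcriptions from source documents (18.1), and the principal investigator checks and signs the data (18.2). The causality call is therefore an investigator's, by inference.

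**The case against.** The best defence reads the three places as one scheme: the administration section is the general rule, the blinding section its exception, and 15.4 the list of what may be supplied when the exception applies. The item after the concentrations in 15.4 is a copy of a partial-unblinding report, which suggests that cases already unblinded are in mind. Detailed routing may sit in the separate IDMC procedures (15.1) or the unblinding manual, neither of which is shown. This reading is possible, but nothing in 15.4 says so, and the administration section admits no exception. The conflict in the text stands.

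Other parts of the defence succeed, and they rule out stronger readings that a reader might infer:

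- *That the investigator would be unblinded.* Release is for a secondary discussion only and as appropriate, and the sender need not read what is sent. The protocol supports could, not would.
- *That every serious adverse event leads to a release.* Such an event convenes the IDMC (14.11.2, 15.3), but concentrations are not among the materials for the primary discussion. The chance of a meeting is not the chance of a release.
- *That one listing exposes the whole trial.* Section 15.4 does not say that all subjects are listed. Registration runs for about 22 months, so during much of the trial some subjects would have no sample on Phase II dosing.
- *That the primary assessment as a whole is compromised.* Only one of the four primary endpoints is defined by causality, and adverse event incidence is summarized by arm with Clopper-Pearson intervals. Daily symptom reports and the Dizziness Handicap Inventory are completed by subjects, or for the daily reports their representatives, and this route does not unblind them.
- *That the key code makes emergency access to concentrations redundant.* The code gives the assignment, not a drug level. The emergency release is a planned safety provision. Its scope needs reconciling, and this review does not say what it should be.

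**Conclusion.** The point holds as a contradiction between sections with a possible consequence for the blind. The administration section, the blinding section and 15.4 cannot all be followed, and as written a readable set of concentrations could pass through the investigator while the trial is running. If that happened, the arm of each listed subject already sampled on Phase II dosing could become known to the person who, by context, judges causality and dose-change permissibility.

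This rests on three assumptions: that placebo subjects have no measurable sirolimus and active subjects generally do; that the sponsor investigator of 15.4 is the principal investigator; and that an investigator makes the causality call. All are reasonable on the text, but the last two are inferences. How often a release would occur cannot be calculated from the protocol.

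**What to change.** - In 15.4 and in Randomization and Blinding, state that any sirolimus concentrations supplied to the IDMC before database lock go directly from the unblinded doctor, or an unblinded CRC, as a closed report that the investigator does not see. The sponsor investigator continues to submit the other materials.
- In Administration of Investigational Products and the Protocol Summary, add the matching exception for the IDMC to the ban on disclosure.
- Reconcile the emergency release in the blinding section with that ban and with the single-subject emergency key procedure, stating for which subject(s) it applies and what the broken-blind condition means.

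The cost is a few sentences in the protocol and a matching line in the IDMC procedure. The unblinded doctor and CRCs already exist and hold the data, and the IDMC loses no information.

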## Criteria of Judgment by the Independent Data Monitoring Committee

[Judgment Criteria]

1) Continuation of the clinical trial will not be authorized if adverse events for which a causal relationship with the investigational products cannot be excluded occur during the trial and fall under either of the following conditions: two or more subjects aged below 18 experience severe adverse event(s); or a subject aged below 18 experiences three or more adverse events. The trial can be continued, however, if the Independent Data Monitoring Committee concludes that there is clear justification and means to maintain safety of remaining subjects.

2) Continuation of the clinical trial will not be authorized if new significant information on safety derived from similar products, research reports, or other sources is considered to be applicable to the trial.

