### Definition of Serious Adverse Events

Seriousness of adverse events is categorized as follows:

1) Non-serious: cases other than 2)

2) Serious: events for which any of the items from a) to g), below, apply.

a) Death

b) Cases that might result in death

c) Any case that requires hospitalization for treatment or prolongs the duration of hospitalization

d) Disability

e) Cases that might result in disability

f) Other medically serious condition for which seriousness is equivalent to a) to e), above

g) Any congenital diseases or abnormalities in the next generation

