### Severity of Adverse Event

Adverse events and severity of each adverse event will be assessed in accordance with the grades below.

[Grading scale for adverse events]

| Grade 1 | Mild; asymptomatic or mild symptoms; clinical or diagnostic observations only; or intervention not indicated. |
| --- | --- |
| Grade 2 | Moderate; minimal, local or noninvasive intervention indicated; or limiting age-appropriate instrumental activities of daily living (ADL)*. |
| Grade 3 | Severe or medically significant but not immediately life-threatening; hospitalization or prolongation of hospitalization indicated; disabling; or limiting self care ADL**. |
| Grade 4 | Life-threatening consequences; urgent intervention indicated. |
| Grade 5 | Death related to adverse event. |

*Instrumental ADL refers to preparing meals, shopping for groceries or clothes, using the telephone, managing money, etc.

**Self-care ADL refers to bathing, dressing and undressing, feeding self, using the toilet, taking medications, and not bedridden.

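### The stopping rule for subjects below 18 counts related serious events in the synopsis and section 14.11.2, but any related adverse events in section 15.5

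*Protocol*

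**What the plan says.** The synopsis and section 14.11.2 item 2 open the rule with the same words: "The clinical trial will be discontinued if serious adverse events for which a causal relationship with the investigational products cannot be ruled out". Two alternative conditions follow. One is met when at least two subjects below 18 have severe events. The other is worded "or a subject aged below 18 experiences three or more adverse events".

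Section 15.5 item 1, which sets the IDMC's criteria, repeats both conditions but opens with "Continuation of the clinical trial will not be authorized if adverse events for which a causal relationship with the investigational products cannot be excluded". The word *serious* is absent.

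All three places let the trial go on if the IDMC finds "clear justification and means to maintain safety of remaining subjects".

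Section 14.11.2 item 1 says when the IDMC must be convened: after any serious event, whatever its cause, "or two or more severe adverse events for which a causal relationship with the investigational products cannot be ruled out".

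Section 14.10.3 defines seriousness by a list of outcomes. Section 14.10.5 defines severity by grade, with Grade 3 as severe.

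**The concern.** A stopping rule should give one answer for one set of data. Here the class of events that counts depends on the section being read. The investigators work from 14.11.2 and the synopsis, and the IDMC from 15.5. No passage explains the difference or says that a narrower rule for the investigators and a broader one for the committee was intended.

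The rule protects children, who are eligible from age seven, in a trial whose primary endpoints are safety and tolerability. It also bears on whether a 16-subject trial continues. At stake is whether a stop is the stated default after severe but non-serious events in minors, or after several non-serious events in one minor.

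**Working it through.** No figure in the plan is in dispute, so the check compares the texts.

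**Step 1. Can an event be severe but not serious?** The serious list in 14.10.3 includes "Any case that requires hospitalization for treatment or prolongs the duration of hospitalization", death, disability, events that might lead to death or disability, and medically equivalent conditions. Grade 3 in 14.10.5 overlaps with this for hospitalization and disability, but its last alternatives are "disabling; or limiting self care ADL". A temporary limitation of self-care that is treated without admission is therefore Grade 3, and it is non-serious unless the investigator judges it equivalent to the listed outcomes. Grades 4 and 5 (life-threatening, fatal) fall on the serious list, so the gap in the severe-event limb lies within Grade 3. The protocol itself keeps the classes apart: 14.11.2 item 1 has separate serious and severe triggers, and 15.4 lists serious-event and severe-event reports as separate committee materials.

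**Step 2. Apply each text to the same data.** All events are related and all subjects are below 18.

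| Case | 14.11.2 item 2 and synopsis | 15.5 item 1 | IDMC meeting required by 14.11.2 item 1 |
| --- | --- | --- | --- |
| Two minors, one severe and serious event each | met | met | yes |
| Two minors, one Grade 3 non-serious event each | not met | met | yes |
| One minor, three non-serious events below Grade 3 | not met | met, read literally | no |

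**Step 3. Is the second case always reviewed?** At least 1 related severe event in each of 2 minors gives at least 2 × 1 = 2 related severe events. The trigger in 14.11.2 item 1 is two or more. Every data set that meets the two-minor limb therefore also convenes the IDMC, which then has 15.5 before it.

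**Step 4. Is the third case always reviewed?** Three non-serious events below Grade 3 include no serious event and fewer than two severe events, so 14.11.2 item 1 is not triggered. The list of occasions in 15.3 does not name this case either, although the principal investigator may call a meeting at discretion. The difference in this limb bites once the IDMC meets for another reason, for example a serious event in any subject.

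**Step 5. A further ambiguity.** Section 14.11.2 item 2 opens with serious events, but its three-event condition refers only to adverse events. It does not say whether each of the three must be serious.

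**Size.** The smallest diverging case in the two-minor limb is 2/16 = 12.5% of planned subjects. In the three-event limb it is 1/16 = 6.25%. These are counts of subjects, not probabilities: the protocol gives neither event rates nor the number of minors expected.

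**The case against.** The strongest reply is that the sections address different people and can both be followed. Section 14.11.2 sets measures for the investigators and 15.5 sets criteria for the committee. Item 2 of 14.11.2 is a sufficient condition for stopping and does not command continuation when it is unmet. With two non-serious Grade 3 events in two minors, item 1 convenes the IDMC, the IDMC applies 15.5, and not authorizing continuation is the default unless the committee justifies going on. On that path the protective result already holds. The committee and its override are the same in every version, and section 15.1 refers to a separate IDMC procedure that may settle the event class.

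Most of this stands. A reader might infer that the sections issue irreconcilable instructions, or that severe non-serious events in minors could escape review. The text supports neither inference.

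The reply does not remove the mismatch. The protocol does not state a two-tier scheme, and two rules with identical conditions and an identical override look like one rule written twice. Investigators reading 14.11.2 or the synopsis see a narrower threshold than the one the committee must apply. A separate procedure cannot correct the protocol's own text. The reply also does not cover the three-event limb, where no meeting is mandatory.

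**Conclusion.** The point holds as an inconsistency in a stated threshold. For related, non-serious Grade 3 events in two minors, 15.5 item 1 is met and 14.11.2 item 2 is not. The consequence there is limited, because review is guaranteed and both texts can be followed. For three related non-serious events in one minor, 15.5 read literally bars continuation even if all three are mild, unless the IDMC overrides; 14.11.2 under its serious lead-in does not, and such events do not by themselves bring the matter to the IDMC. A reader might infer that three mild events would halt the trial automatically. They would not, because the 15.5 criterion operates only when the committee meets, and it carries the override.

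This rests on two assumptions: that a self-care limitation treated without admission is not classed as serious by medical equivalence, and that the separate IDMC procedure, which is not at hand, does not replace the protocol's wording. How often these cases would arise cannot be estimated from the protocol. Because the rule protects children and the remedy is wording, it should be corrected.

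**What to change.** Use one rule in the synopsis, section 14.11.2 item 2 and section 15.5 item 1.

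- **Two-minor limb:** count related severe events (Grade 3 or higher), whether serious or not. This matches the severe-event trigger in 14.11.2 item 1. Keep the IDMC override.
- **Three-event limb:** state the seriousness or minimum grade that each of the three events must have, and use it in all three places. Add this condition to the occasions that convene the IDMC, so that meeting it always leads to review.
- **IDMC procedure:** align the separate document with the chosen wording.

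If the sponsor does intend a narrower rule for the investigators than for the committee, the protocol should say so and give the reason.

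The cost is wording, with no new data or visits. The stop condition in the synopsis and 14.11.2 becomes somewhat broader, and the override limits the effect of that.
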